## Methods/design

### Study design

The study design is a prospective, single-blind randomized controlled trial. Three intervention programs, namely, a WBV exercise program, lower extremity RT, and a health education program, will be included in the study (Fig. 1). This study will be conducted at the Sport Medicine and Rehabilitation Center, Shanghai University of Sport. The power analysis with settings at *α* = 0.05, power (1 − *β*) = 0.80 and effect size = 0.25 showed that three groups of 120 participants in total was the required sample size. Given the dropouts, we decided to recruit 180 participants for the research. A total of 180 patients from community centers in Yangpu District, Shanghai, China will be included through advertisements placed in various community centers by the recruiter. A multidisciplinary team composed of clinicians, physiotherapists, and exercise specialists will run the program.

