**Fig. 1 Fig1:**
[figure not shown]
Flow diagram of study design

Prior to the initiation of the study, all participants will fill out the questionnaire with their details, including medical history and past and present job status. Participants will also complete the Mini-Mental State Examination and the Activities of Daily Living test, and will describe their exercise habits (frequency and duration). Informed consent will be requested from each participant prior to the inclusion in the study.

Participants who meet all study inclusion criteria and consent to participate will be randomly allocated to the WBV exercise, lower extremity RT, and health education groups via using computer-generated randomization by a research designer. The study nurse will assign participants to the interventions. Only the research designer and trainers will know the randomized assignments. The assessors will be unaware of the randomization and will not be involved in the exercise interventions. This study will include assessments at the following time points: before intervention, after 3 months of intervention, and after 3 months of further follow-up with no active intervention. The total study period will be 6 months. Additional files 1 and 2 represent SPIRIT Checklist, and schedule of enrollment, interventions and assessments﻿.

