### Statistical analysis

SPSS for Windows, version 17.0 (SPSS Inc., Chicago, IL, USA) will be used for statistical analysis. If any participant withdraws from the trial, the missing values will be replaced by the last assessment score of the participant. And all available data will be analyzed using an intention-to-treat analysis. Chi-squared tests will be used to test for demographic differences among the WBV training, RT, and control groups.

An intention-to-treat analysis will be performed by including all participants in the analysis according to the original group allocation. The follow-up will be maximized regardless of the program attendance. Repeated-measurement analysis of variance will be used to evaluate for between- and within-group difference. Bonferroni’s post hoc test will used for comparing the results. Data will be presented as the mean and standard deviation, and significance will be set at 0.05.

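### The 120 participants said to give 80% power at effect size 0.25 do not follow from the stated inputs, and that power is not shown for the post-treatment comparison

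*Protocol article*

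**What the plan says.** Under Study design, the protocol article gives alpha 0.05 and power 0.80, and reports that "effect size = 0.25 showed that three groups of 120 participants in total was the required sample size". It then adds a margin: "Given the dropouts, we decided to recruit 180 participants for the research". Participants are "randomly allocated to the WBV exercise, lower extremity RT, and health education groups", with no allocation ratio given. Assessments are set at baseline, at 3 months (end of intervention) and at 6 months (follow-up).

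Under Statistical analysis, the planned test is a repeated-measures ANOVA: "Repeated-measurement analysis of variance will be used to evaluate for between- and within-group difference". Bonferroni post hoc comparisons follow, and "significance will be set at 0.05". No analysis adjusted for the baseline value is described. Neither section says which F test, how many measurements or what correlation lies behind the 120.

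**The concern.** The article prints inputs and a result that do not match on the simplest reading. With three groups, f = 0.25 and alpha 0.05, a comparison at one time point needs clearly more than 120 for 80% power. The route that does return 120 under the planned type of analysis is the group main effect, averaged over all occasions. In a randomised trial this average includes a baseline at which the arms have no expected difference, so it dilutes the treatment effect.

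At stake is how the result will be read. The plan implies that 80% power survives even if only 120 of 180 remain. If the power for the difference after treatment is lower, a null result from about 120 completers would be taken as adequately powered without support.

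**Working it through.** **Inputs.** From Study design: alpha 0.05, power 0.80, effect size 0.25, three groups, total 120, recruited 180. From Study design and Outcome measures: three assessments. Assumed: 0.25 is Cohen's f; equal allocation; equal variances and a common correlation ρ between occasions. N is searched in multiples of 3. Power is from the noncentral F distribution with noncentrality λ.

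**1. Reproducing 120.** For the group main effect of a repeated-measures ANOVA with m occasions, λ = f²·N·m / [1 + (m − 1)ρ], with 2 and N − 3 degrees of freedom.
- m = 2, ρ = 0.5: λ = 0.0625 × 120 × 2/1.5 = 10.0, power 80.5%. N = 117 gives 79.4%, so 120 is the exact minimum.
- m = 3 (as planned), ρ = 0.5: the minimum is 108, and 120 gives 85.1%.
- m = 3, ρ = 0.7: the minimum is 129, and 120 gives 77.7%.

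For a baseline-adjusted ANCOVA, λ = f²·N / (1 − ρ²), with 2 and N − 4 degrees of freedom. At ρ = 0.5, λ = 7.5/0.75 = 10.0, and the minimum is again 120 (80.5%).

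**2. Using only the stated inputs.** For a three-group F test at one time point, λ = f²·N, with 2 and N − 3 degrees of freedom.
- N = 120: λ = 7.5, power 67.6%.
- N = 159: power 80.5% (the minimum).
- N = 180: power 85.5%.

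**3. Taking f = 0.25 as the difference after treatment.** The arms are equal in expectation at baseline, so averaging over occasions shrinks f for the main effect to 0.25 × (m − 1)/m if the effect persists. At N = 120 and ρ = 0.5:
- m = 2: f = 0.125, λ = 0.015625 × 120 × 2/1.5 = 2.5, power 27%.
- m = 3: f = 0.1667, λ = 0.02778 × 120 × 3/2 = 5.0, power 49%.

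Conversely, for the averaged f to be 0.25, the post-treatment f would have to be 0.25 × 2 = 0.50 (m = 2) or 0.25 × 3/2 = 0.375 (m = 3).

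For the group-by-time test with the same post-treatment effect, λ = f²·N·[(m − 1)/m] / (1 − ρ), with 2(m − 1) and (N − 3)(m − 1) degrees of freedom. Power at N = 120:

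| ρ | two occasions | three occasions, effect persisting |
|---|---|---|
| 0.3 | 52% | 54% |
| 0.5 | 68% | 71% |
| 0.6 | 78% | 81% |
| 0.7 | 89% | 92% |

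At ρ = 0.5 and two occasions, λ = 7.5 × 0.5/0.5 = 7.5, the same as the one-time-point test, so the minimum is again 159. With three occasions it is 147.

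**4. Margin.** From 180 to 120 is a loss of 60/180 = 33%. From 180 to 159 it is 21/180 = 11.7%.

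**The case against.** The strongest reply is that no section calls the calculation one-way, so 159 may be the wrong yardstick. The plan is a repeated-measures ANOVA, and a standard version of it returns exactly 120. With the three planned assessments, and 0.25 taken as the averaged effect, 120 gives at least 80% up to ρ of about 0.63. If 0.25 is instead the interaction effect on the scale λ = f²·N·m/(1 − ρ), at most 81 are needed. The article does not define 0.25 as the post-treatment difference, so the 27% rests on a reading it does not state. Finally, 180 are recruited, and even the one-way test has 85.5% at 180.

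Most of this stands. It rules out the stronger inference, tempting from 159 against 120, that the article contains a plain arithmetic error or that the trial is underpowered. The documents support neither: the test is unnamed, a standard calculation gives 120, and a high enough correlation gives 80% or more.

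It does not rescue the figure as a justification. The matching routes reach 120 by giving 0.25 a more demanding meaning (a post-treatment f of 0.375 to 0.50 for the main effect, and 0.50 for the two-occasion interaction, since 2f² = f²(post)/2) or by an analysis that is not planned. The exact main-effect match also uses two occasions where three are planned.

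A reader might also fault the absent dropout rate, the unnamed outcome and the lack of power for the Bonferroni comparisons. The first two are details that an article may leave to the full protocol. The third is a design preference, since no pairwise power is claimed.

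**Conclusion.** The concern holds in a limited form. From the inputs printed, 120 does not follow: 159 are needed, and 120 gives 68%. It follows only with an unstated correlation, and then for a main effect that mixes in the baseline or for an ANCOVA that is not planned. For a post-treatment f of 0.25, 80% power at 120 is not shown. At ρ = 0.5 it is 27% to 49% for the main effect and 68% to 71% for group-by-time. It is attainable for group-by-time at ρ of roughly 0.6 or more.

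This rests on reading 0.25 as Cohen's f, equal arms, a common correlation and, for the three-occasion figures, an effect that persists to 6 months. The issue is moderate: it concerns the power statement and the choice of contrast, and the recruitment target of 180 need not change.

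**What to change.** Keep 180 and change the basis of the calculation.

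- **Preferred:** make the between-group comparison an analysis of the post-treatment value with the baseline value as covariate. State that 120 analysed participants give 80% power for f = 0.25 only if the baseline-to-follow-up correlation is at least about 0.5.
- **If the repeated-measures ANOVA is kept:** name the group-by-time test as the one that is powered, and restate its power with the assumed correlation and the three planned occasions.
- **If no correlation can be justified:** state that 159 analysed participants are needed, that 180 allows 11.7% loss, and that power is 68% if only 120 are analysed.

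The cost is wording and some analysis work. No further participants or measurements are needed, because the baseline values are already collected. The drawback is that the stated power and tolerance for loss become less favourable, or depend openly on a correlation.

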**Fig. 1 Fig1:**
[figure not shown]
Flow diagram of study design

Prior to the initiation of the study, all participants will fill out the questionnaire with their details, including medical history and past and present job status. Participants will also complete the Mini-Mental State Examination and the Activities of Daily Living test, and will describe their exercise habits (frequency and duration). Informed consent will be requested from each participant prior to the inclusion in the study.

Participants who meet all study inclusion criteria and consent to participate will be randomly allocated to the WBV exercise, lower extremity RT, and health education groups via using computer-generated randomization by a research designer. The study nurse will assign participants to the interventions. Only the research designer and trainers will know the randomized assignments. The assessors will be unaware of the randomization and will not be involved in the exercise interventions. This study will include assessments at the following time points: before intervention, after 3 months of intervention, and after 3 months of further follow-up with no active intervention. The total study period will be 6 months. Additional files 1 and 2 represent SPIRIT Checklist, and schedule of enrollment, interventions and assessments﻿.

### Participants

#### Inclusion criteria

Participant selection will be based on the classification criteria of the American Rheumatism Association for KOA [27]:Men or women with radiographic diagnostic criteria of definite KOA (unilateral or bilateral), with reports of pain symptoms for at least 3 monthsMild-to-moderate KOA (Lequesne Knee Score = 1 to 7)Age 50–70 yearsMedication not expected to change during the study periodAvailability: three times a week over 3 months

#### Exclusion criteria

Exclusion criteria include the following:Knee surgery in the past 6 monthsAcute symptomatic OAA minimum pain intensity score of more than 7 on a Visual Analog Scale (VAS)Other muscular, joint, or neurological conditions that affect lower limb functionUnable to walk unaidedCurrently undertaking a structured exercise program for KOAAlzheimer’s disease, Parkinson’s disease, and motor neuron disordersDiabetes mellitus, cardiac or respiratory insufficiency, and inability to understand the procedure

#### Withdrawal criteria and management

Withdrawal from the study will be allowed based on the following:The participant makes such a requestThe participant develops a serious disease, such as heart disease or stroke, and continuing their participation becomes inappropriate in the opinion of the investigatorThe participant has an adverse reaction related to the WBV exercise or lower extremity RT

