**Methods/design:**

We will conduct a prospective, single-blind randomized controlled trial on 180 KOA patients. Participants will be randomly assigned to the WBV exercise, lower extremity resistance training, and health education groups. The WBV exercise group will participate in a 12-week WBV training. The lower extremity resistance training group will undergo a 12-week lower extremity resistance training of both lower limbs. The control group will receive health education for 12 weeks. After the intervention, the participants will be followed up for 3 months with no active intervention. Primary outcome measures will include anthropometric measurements, gait analysis during walking and stair climbing, muscle strength test of the knee and ankle, proprioception test of the knee and ankle, and neuromuscular response of the leg muscles. Secondary outcome measures will include self-reported pain and physical functional capacity, and physical performance measures. Furthermore, adverse events will be recorded and analyzed. If any participant withdraws from the trial, intention-to-treat analysis will be performed.

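### Withdrawal from the study is allowed for a reaction to the exercise, a ground open only to the exercise arms; with the last score carried forward, a worsening can be recorded as no change

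*Protocol article*

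**What the plan says.** The section Withdrawal criteria and management opens with "Withdrawal from the study will be allowed based on the following" and lists three grounds. Two can arise in any arm: the participant's own request, and serious disease that in the investigator's opinion makes continuing inappropriate. The third is that the "participant has an adverse reaction related to the WBV exercise or lower extremity RT". The article describes no separate status for someone who stops training but remains under assessment.

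The Statistical analysis section makes three statements that bear on such a person:

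- On people who miss sessions, it says: "The follow-up will be maximized regardless of the program attendance".
- If someone withdraws, "the missing values will be replaced by the last assessment score of the participant".
- On who is analysed, it says: "An intention-to-treat analysis will be performed by including all participants in the analysis according to the original group allocation".

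Study design fixes the assessments at three times: "before intervention, after 3 months of intervention, and after 3 months of further follow-up with no active intervention". Training fills the 12 weeks between the first and the second. The abstract adds that "adverse events will be recorded and analyzed".

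**The concern.** Stopping an intervention and leaving a trial are different events, and an intention-to-treat analysis depends on keeping them apart. Here a reaction to the exercise, which is naturally a reason to stop exercising, is listed as a ground for leaving the study. Someone who stops training after a reaction is also a plain case of non-attendance, for whom the analysis section wants follow-up maximised. Staff are not told which rule takes precedence.

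Three features combine to make this matter for the estimate:

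- The ground is tied to WBV and RT, so it can produce missing data in two of the three arms only.
- The reason for missingness may be related to the outcome.
- No assessment falls between baseline and month 3, so the carried-forward value for anyone who leaves during training is baseline.

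At stake are the WBV-versus-education and RT-versus-education comparisons, and knowledge of the 3- and 6-month outcome status of participants who reacted to the exercise.

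**Working it through.** The plan gives no figure on this point: no adverse-reaction rate, no expected outcome for those who react, and no dropout rate. The only indirect figure is the increase from 120 to 180 participants, which implies an allowance of 1 − 120/180 = 33.3% for loss of every kind. It cannot be split by reason or by arm.

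**Step 1: which value is analysed.** A participant withdrawn for a reaction during the 12 training weeks has one assessment, at baseline. Carrying the last score forward gives baseline at month 3 and at month 6, so the recorded change is 0 at both.

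**Step 2: the bias in one arm.** Count improvement as positive. Let *w* be the share of the arm withdrawn on this ground before month 3, *δ* their true mean change and *d* the mean change of the rest, in SD units.

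- True arm mean = (1 − *w*)·*d* + *w*·*δ*
- Arm mean with baseline carried forward = (1 − *w*)·*d* + *w*·0
- Bias = carried-forward mean − true mean = −*w*·*δ*

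The value of *d* cancels. Check with *w* = 0.10, *d* = 0.50, *δ* = −0.50: true mean 0.45 − 0.05 = 0.40; carried-forward mean 0.45; bias +0.05.

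**Step 3: a range.** All values of *w* and *δ* are assumptions.

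| Share withdrawn | *δ* = −1.0 SD | *δ* = −0.5 SD | *δ* = 0 | *δ* = +0.25 SD |
|---|---|---|---|---|
| 5% | +0.050 | +0.025 | 0 | −0.013 |
| 10% | +0.100 | +0.050 | 0 | −0.025 |
| 15% | +0.150 | +0.075 | 0 | −0.038 |

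Positive entries flatter the exercise arm; negative entries work against it. If the 180 participants are allocated equally (a ratio is not stated), each arm has 60, and 5–15% is 3 to 9 people.

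**Step 4: from arm to comparison.** The bias in a difference between arms is the difference between the arm biases. This ground contributes nothing in the education arm, so for exercise versus education its contribution is the table entry. Withdrawals by request or for serious disease can occur in every arm, and carry-forward adds its own bias there; the table leaves this out. For WBV versus RT, the contributions cancel to the extent that *w*·*δ* is similar in the two arms.

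**The case against.** The strongest case on the other side has five parts.

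- **The rule is permissive.** Withdrawal is allowed, not required. A participant who reacts may stop the sessions and still be assessed, so both sections can be followed. This stands. A reader might infer a flat contradiction, but the text supports only a tension: the sections pull apart once such a participant is actually withdrawn, and nothing says when that should happen.
- **Nobody leaves the analysis.** A reader might infer that poor outcomes are removed or that the intention-to-treat label is false. The documents do not support this: everyone is analysed as allocated, with missing values filled. What is lost is the true post-baseline value, not the participant.
- **The direction is not known.** A reader might infer a bias in favour of exercise. That needs the withdrawn participants to have worsened on the listed outcomes, and the article does not link a reaction to strength, proprioception, gait or muscle latency. This stands too, and it is why the table includes zero and negative entries.
- **Safety recording is not cancelled.** A reader might infer that adverse-event follow-up ends at withdrawal. The abstract promises recording and analysis without excepting those who withdraw, and the reaction that prompts withdrawal is already known. The point is limited to the 3- and 6-month outcome assessments.
- **An article condenses.** The full protocol may separate stopping exercise from ending follow-up. That would excuse silence. Here, however, the article states a rule, at the level of the study, and pairs it with a stated imputation rule. The point rests on what is written.

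**Conclusion.** The point holds in a limited form. The article allows study-level withdrawal on a ground that only the WBV and RT arms can meet, in tension with its promise to maximise follow-up. For a participant withdrawn before month 3, carry-forward then records no change whatever the truth, so a worsening in an exercise arm would be masked.

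The size is illustrative. With 5–15% of an arm withdrawn on this ground and a true worsening of 0.5–1 SD, the arm's mean change is overstated by about 0.025–0.15 SD. With no true change the bias is zero; with a true improvement of 0.25 SD the arm is understated by about 0.013–0.038 SD. The shares and the true changes are all assumptions, because the documents supply neither. The mechanism itself rests only on the stated assessment times and the stated imputation rule. It deserves correction because the remedy is cheap and replaces an unverifiable assumption with observed data.

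**What to change.** Reconcile Withdrawal criteria and management with Statistical analysis by stating four things:

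1. Stopping the exercise does not by itself end outcome follow-up.
2. Participants who stop because of an exercise-related reaction are still invited to the scheduled 3- and 6-month assessments, unless they withdraw consent or the investigator judges continued participation inappropriate.
3. Their observed values are analysed in the arm to which they were randomised.
4. Reasons for stopping exercise and for leaving the study are reported by arm.

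The clinical criteria for stopping exercise and the serious-disease ground stay unchanged. The investigator's judgement has to be kept, because the assessments include repeated maximal contractions and unexpected ankle perturbations.

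The cost is about a paragraph of protocol text and some visits already in the schedule. On the illustrative 3 to 9 participants per exercise arm, that is at most 2 × 3 = 6 to 2 × 9 = 18 visits per arm.

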#### Participant recruitment

Participants will be recruited through advertisements placed in community centers and distributed to health care providers (medical practitioners, rheumatologists, and physiotherapists). Participants who satisfy the inclusion criteria will be contacted by the same investigator to confirm their willingness to take part in the trial and to arrange the baseline assessment of outcomes. Participants will provide written informed consent before the baseline assessment.

### Interventions

#### WBV exercise group

Participants in the WBV exercise group will participate in their training program 3 days per week with at least 1 day between each session for 12 weeks. WBV training will be conducted using a vibration device (AV001; BODYGREEN, Xiushui Township, Taiwan). The participants will stand with slightly bent knees (30°) on the platform and without shoes. Each session of WBV exercise will last 30 min (60 s for vibration, and 60 s for rest). The vibration parameters in the WBV training group will as follows: frequency (35–40 Hz), amplitude (4–6 mm), and acceleration ranged from (2–5 g). These parameters were considered sufficient by Delecluse for achieving the desired physiologic effects [28].

